**Protocol Synopsis**

Title: Effects of HIV self-testing on testing promotion and risk behaviours reduction among transgender women: a randomized controlled trial in China

**Primary Objective**

To evaluate the efficacy of the intervention (HIV self-testing, HIVST) in increasing HIV test numbers among transgender women (TGW) during six months of follow-up.

**Secondary Objectives**

- To evaluate the efficacy of HIVST in increasing HIV tests numbers during three months of follow-up.
- To evaluate the efficacy of HIVST in increasing HIV testing proportion during six months of follow-up.
- To evaluate the efficacy of HIVST in increasing HIV testing proportion during three months of follow-up.
- To evaluate the efficacy of HIVST in changing the partner numbers during six months of follow-up.
- To evaluate the efficacy of HIVST in changing the frequency of condomless sex during six months of follow-up.

**Hypothesis**

The primary hypothesis is that HIVST can improve regular HIV testing behavior among TGW.

**Primary Outcome:** The mean changes in the number of HIV tests among TGW during six months of follow-up.

**Secondary Efficacy Outcomes:**

- The mean changes in the number of HIV tests during three months of follow-up.
- The proportion of HIV testing at six months.
- The proportion of HIV testing at three months.
- The mean changes in partner numbers during six months of follow-up.
- The mean changes in the frequency of condomless sex during six months of follow-up.

**Study Design:** This study is an open-label, randomized controlled trial. Eligible participants for screening are HIV-negative TGW. The minimum expected total recruitment of TGW is approximately 230, with a minimum expected recruitment of approximately 115 participants in the intervention group and the control group.

**Sample Size:** We used PASS V. 15.0 (NCSS, LLC. Kaysville, Utah, USA) to calculate the sample size based on a repeated measures design with two time points. Enrolment of 103 participants per group was projected to provided 90% power to detect a mean difference of 0.35 in the number of HIV tests per three months^1^ between groups (two-tailed α = 0.05). At least 115 patients per group were needed assuming an anticipated 10% dropout rate.

**Summary of Participants Eligibility Criteria:** The following are inclusion criteria for candidates: being 18-65 years of age, assigned male at birth and self-identifying as female, no previous record of HIV positive test results, tested negative for HIV antibodies in the rapid test during the screening, engaged in sexual activity in the past six months, willing to provide truthful information about their sexual behaviour, own a smartphone and able to use WeChat, and provide electronic informed consent. The following are the exclusion criteria for candidates: candidates who do not meet the defined inclusion criteria, encompassed a positive HIV status prior to enrolment and refusal to partake in the study.

**Intervention Contents:**

**Quadruplex self-testing package:** The quadruplex self-testing kits to be used (Wondfo Guangzhou, China) are finger stick-based, which can detect HIV-1 antibody, Treponema pallidum antibody, Hepatitis B surface Antigen, and Hepatitis C virus antibody in blood specimens at 6 weeks after infection. The kits will be packaged with the required consumables during finger blood sample collection (a disposable retractable safety lancets, alcohol pad, capillary tube, Wondlfo solution, and a sealed bandage). Each package will contain corresponding identification numbers and instructions for the testing procedure, results interpretation, and results upload.

**Procedures:**

After including TGW who test negative for HIV and meet the eligibility criteria, they will be randomly assigned to the intervention group and the control group. Based on participants' needs, the intervention group will have the opportunity to apply for free HIV self-testing (HIVST) kits and mailing services every three months (via WeChat). Participants can request to receive 1-5 self-testing kits based on their own needs. HIV-related health information will be regularly sent to both the intervention and control groups at predetermined intervals (at enrolment and three months after enrolment). Follow-up surveys will be conducted, and electronic questionnaires will be filled out at three months and six months after enrolment. To protect personal privacy, all HIV self-testing kits mailed to participants will be discreetly packaged in an unmarked box along with the instructions. Each self-testing kit will be assigned a unique code for future tracking and result retrieval. Users of the self-testing kits can scan the QR code on the instructions, take a photo of the self-test result, and anonymously upload it to the online platform (created through the online questionnaire platform: https://jinshuju.net/home).

**Statistical Considerations:**

**General Considerations**

A summary of the demographic and behavioural characteristics of the participants will be provided. Descriptive statistics for continuous variables will include the mean and standard deviation (if they follow a normal distribution) or the median and interquartile range (if they do not follow a normal distribution). For categorical variables, frequencies and percentages will be reported.

The Intention-to-Treat Set (ITT) is defined as all randomized participants. All efficacy analyses will be performed based on the ITT population.

**Analysis of the Primary and Secondary Efficacies**

Net differences in mean changes from baseline in outcome variables between groups will be analysed using covariance analysis, with group as a factor and baseline value as a covariate. A step-down approach will be used to find a significant result; the primary and secondary outcomes are to be tested sequentially to control the familywise type I error rate according to the following order: mean changes in the number of HIV tests at six months (primary outcome), mean changes in the number of HIV tests at three months, mean changes in the sexual partner number at six months, and mean changes in the frequency of condomless sex at six months. Statistical significance (two-sided P<0.05) at each step is required to test the next hypothesis. Linear mixed-effects model with individuals as a random effect will be used to evaluate the main effects of the intervention and interaction effects of time on the primary outcome. Statistical analysis will be conducted using R software. For a detailed description of the statistical analysis methods, please refer to Section 10.

**Study Glossary**

| Abbreviation or Term | Definition/Explanation |
| --- | --- |
| CBOs | Community-Based Organizations |
| CI | Confidence Interval |
| HIV | Human Immunodeficiency Virus |
| HIVST | Human Immunodeficiency Virus Self-Testing |
| ITT | Intention-To-Treat Analysis Set |
| QR | Quick response |
| RCT | Randomized Controlled Trial |
| TGW | Transgender Women |

**1. OBJECTIVES**

**1.1 Primary Objective**

To evaluate the efficacy of the intervention (HIV self-testing, HIVST) in increasing HIV test numbers among transgender women (TGW) during six months of follow-up.

**1.2 Secondary Objectives**

- To evaluate the efficacy of HIVST distribution in increasing the mean changes in the number of HIV tests during three months of follow-up.
- To evaluate the efficacy of HIVST in increasing HIV testing proportion during six months of follow-up.
- To evaluate the efficacy of HIVST in increasing HIV testing proportion during three months of follow-up.
- To evaluate the efficacy of HIVST in changing the partner numbers during six months of follow-up.
- To evaluate the efficacy of HIVST in changing the frequency of condomless sex during six months of follow-up.

**2. BACKGROUND AND RATIONALE**

The term "transgender" refers to individuals whose gender identity and expression differ from the sex they were assigned at birth, regardless of whether they have undergone medical interventions such as gender-affirming surgeries, hormone therapy, facial reconstruction, etc. Within the transgender population, there are two main categories based on self-identified gender: transgender women (TGW) and transgender men (TGM). TGW refers to individuals who were assigned male at birth but identify and express themselves as female^2^. TGW are a key population for HIV infection globally. A meta-analysis of HIV infection among transgender women worldwide showed an average HIV prevalence rate of 19.1%. The risk of HIV infection among transgender individuals is 48.8 times higher compared to the general population^3^. However, the extreme sense of shame, discrimination, and fear of positive results often experienced by transgender individuals often leads to their reluctance to seek healthcare or social services^4^, resulting in lower HIV testing rates^5,6^. To achieve the goal of ending the HIV/AIDS epidemic by 2030, there is an urgent need to optimize the HIV prevention and treatment strategies for TGW at present.

Globally, only 65.3% of the TGW has undergone HIV testing, with 66.6% of TGW in the United States being tested for HIV ^6^. In China, only 34.6% of the TGW has undergone HIV testing ^7^. In some low- and middle-income countries, the proportion of HIV-tested TGW is less than 50%, such as 27.0% in Brazil, 43.6% in Thailand, and 43.9% in Vietnam^8-10^. The proportion of TGW aware of their HIV infection status is still far from the first 90% target, highlighting the urgent need to explore effective strategies to expand testing and meet the testing needs of the transgender population^2^ .

HIV self-testing (HIVST) offers convenience, privacy, and ease of use^11^. It eliminates some typical barriers to testing, such as inconvenience (related to transportation, time, and location), privacy concerns, and stigma^12^, providing TGW with a non-discriminatory opportunity for HIV testing. The use of HIVST is supported by the World Health Organization, particularly for populations with low healthcare service coverage, high risk of HIV infection, and limited access to HIV testing services^13^. Previous studies have found that HIVST not only increases testing frequency among men who have sex with men (MSM)^14^, but also increases testing frequency among male truck drivers^15^, female sex workers^16^, and women and their male partners seeking antenatal care^17^. HIVST has shown high acceptance rates among TGW and has facilitated HIV testing among their sexual partners and those who have never been tested before^18-21^.

While global health organizations, including the World Health Organization, recognize transgender individuals as a distinct and special population, many researchers consider TGW as a subgroup of men who have sex with men (MSM). Epidemiological surveys often combine MSM and TGW regardless of gender identity and sexual orientation, which may blur how TGW acquire HIV and whom they may transmit the infection to^22^. Studies have shown that the sexual networks of TGW and their partners may differ from those of MSM, and TGW have different characteristics compared to cisgender men who have sex with men^23^. Therefore, there is currently a lack of urgently needed interventions specifically targeting TGW, such as HIV testing promotion programs^24^.

In summary, HIVST has shown good acceptance and significant potential for development in the TGW due to its convenience, confidentiality, and privacy. However, there is a lack of randomized controlled studies both domestically and internationally that utilize HIVST to promote HIV testing among TGW.

**2.1 Hypotheses**

We hypothesized that HIVST can improve regular HIV testing behavior among TGW.

**3. IMPLEMENTATION PLAN**

**3.1 Study Design**

This study is an open-label, randomized controlled trial. Participants who meet the inclusion criteria are recruited in Shenyang and Beijing through a combination of online and offline methods. Participants are randomly assigned in a 1:1 ratio to either the intervention group or the control group. The researchers provide the intervention group TGW with a link to apply for HIV self-testing kits, with each participant being able to request 1-5 kits as needed. The application link is provided only at the time of enrolment and at three months after enrolment. The researchers conduct electronic questionnaire surveys with the participants at baseline, three months after enrolment, and six months after enrolment to analyse the impact of HIV self-testing on HIV testing behaviour among TGW.

The overall study design is described by a flow chart as follows (Figure 1):

[figure not shown]

**Figure 1 Flow chart of study design**

**3.2 Number of Study Sites**

This study is an online intervention survey research that will recruit participants in two cities in northern China, Shenyang and Beijing.

**3.3 Replacement of Participants**

There will be no replacement for participants.

**3.4 Estimated Study Duration**

**3.4.1 Study Duration for Participants**

The plan is to recruit participants from January 2021 to June 2021. For all participants involved in the study, the duration of the study after enrolment is six months.

**3.4.2 End of Study**

Primary Completion: The primary completion date refers to the point at which the last participant is assessed or receives intervention for the final collection of data for the primary endpoint(s), whether the study concluded as planned in the protocol or was terminated early.

The primary completion date is the same as the end-of-study date and is the date when the last enrolled participant has completed the end-of-study visit (month 6) (i.e., the last participant's last visit).

If the study concludes prior to the primary completion date originally planned in the protocol (i.e., early termination of the study), then the primary completion date corresponds to the last subject’s last visit.

End of Study: The end of the study date is defined as the last enrolled participant’s completion of the end-of-study visit (month 6) or terminates of the study early. Terminating early means that enrolled participants complete the study visit ahead of schedule.

**4. PARTICIPANTS' ELIGIBILITY**

Investigators will be required to have a screening log of all potential study candidates that include limited information about the potential candidate, such as the screening date. This log can be completed and updated through an online survey platform (https://jinshuju.net/home).

Before conducting any research-related procedures, appropriate digital informed consent (and, where applicable, assent) must be obtained (see Section 12.1).

**4.1 Inclusion and Exclusion Criteria**

**4.1.1 Inclusion Criteria**

- Aged 18 to 65 years old.
- Assigned male at birth, and self-identifying as female.
- Tested negative for HIV antibodies during the screening at enrolment.
- Engaged in sexual activity in the past six months.
- Willing to provide truthful feedback on their sexual behaviour.
- Owns a smartphone and is able to use WeChat.
- Willing to sign an informed consent form.

**4.1.2 Exclusion Criteria**

- Unwilling to participate in follow-up.
- Encompassed a positive HIV status prior to enrolment.
- Refused to use HIV self-testing (HIVST).

**5. RANDOMIZATION AND MASKING**

Randomization will be performed based on a computer-generated random sequence using SPSS software version 26.0 (SPSS, IBM Inc) with a random seed of 230. The sequence will be divided into two groups by the Visual Binning function. Enrolment will be ongoing during the trial period. Due to the different intervention approaches between the two groups, blinding was not feasible for CBO staff and participants.

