**6. PARTICIPANTS ENROLLMENT**

Before initiating specific research activities/procedures, all participants must personally sign the digital informed consent form. Each participant has been assigned a unique identification number, which will be used throughout the study to identify the individual and must be used in all research-related documents pertaining to that participant. This identification number must remain unchanged throughout the study; it should not be altered, including during re-screening of participants, after the initial assignment.

**Confirmation of TGW identity:** The study participants' transgender female identity is verified through a logical screening process using self-identified gender questions in the baseline questionnaire. Researchers rigorously assess the identity of the participants. If there are doubts about the identity of a participant, an additional identity confirmation questionnaire is sent, which includes questions about transgender-related knowledge. Additionally, the following methods are used to corroborate their identity: contacting the participant's recruiter to request identity verification evidence, reviewing the participant's social media posts for identity-related clues or evidence, and requesting the participant to provide recent photos of themselves presenting in feminine attire.

When the researchers determine that a participant meets the inclusion criteria, the investigator should record this decision and the date in the digital Case Report Form (CRF).

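### Section 5 prints the randomisation seed and describes no allocation concealment in an open-label trial; separately, adding city to the fixed model would bring a modest gain in precision

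*Protocol*

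**What the plan says.** **Allocation.** Protocol Section 5 describes a "computer-generated random sequence using SPSS software version 26.0 (SPSS, IBM Inc) with a random seed of 230". It continues: "The sequence will be divided into two groups by the Visual Binning function". It adds that "Enrolment will be ongoing during the trial period" and that "blinding was not feasible for CBO staff and participants". Section 3.1 gives the ratio as 1:1, and the Synopsis gives a minimum of about 230 participants, 115 per group. Neither Section 5, nor Section 6 on enrolment, nor Section 7.4 on procedures says who keeps the list or how the next assignment is hidden from those who enrol.

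**Entry.** Section 6 states: "Researchers rigorously assess the identity of the participants". Where there is doubt, the checks include an extra questionnaire, evidence from the recruiter, social media posts and photographs. Sections 4.1.1 and 4.1.2 add criteria that rest on stated willingness.

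**City.** Under Section 3.2 the study "will recruit participants in two cities in northern China, Shenyang and Beijing". Section 5 mentions no strata. Section 10.3.2 fixes the analysis of covariance with group and baseline value only. It gives the mixed model a random effect for individual and no city term. City is not among the six subgroup factors in Section 10.3.3.

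**The concern.** A seed is the input that concealment is meant to protect. Printing it next to the software version and the splitting method in the working protocol goes further than leaving concealment undescribed. It matters more here because staff are not blinded, enrolment is sequential, some entry criteria call for judgement, and the HIV testing outcome relies on participants' reports (Section 10.3.1). Someone who knew the next arm could influence who is admitted. Adjusting for the baseline number of tests would not remove selection on an unmeasured trait such as motivation to test.

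The city question is separate and smaller. One list with no stated strata serves two cities, so the arms may differ in city mix by chance. The model as fixed does not use a factor that is known for every participant.

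**Working it through.** **1. What someone would need to rebuild the list.**
- Stated: SPSS 26.0, seed 230, Visual Binning, 1:1 ratio, and a list length of about 230.
- Not stated: the generator option, the random function, the exact list length, the cut point, which bin is which arm, and how list positions map to participants.

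A demonstration outside SPSS shows why both lists matter. With seed, generator and splitting rule all fixed, two runs agreed on 100% of 230 assignments. The same seed under a different generator agreed on 53%, about chance. Lengthening the list from 230 to 240 left the first 230 assignments unchanged in that example. So the seed alone is not enough, but most of the missing settings have few plausible values. No list was regenerated in SPSS.

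**2. Order of steps.** The Synopsis and Section 7.4 place assignment after inclusion of eligible participants, and Section 6 requires the eligibility decision and its date in the case report form. No section says that the baseline questionnaire must be submitted before the arm is known, or that whoever judges eligibility cannot see the next assignment. Order of steps is not concealment.

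**3. Dates.** Section 3.4.1 plans recruitment for January to June 2021. Reference 16, on secondary distribution of self-tests, is dated 2023. This text is therefore later than planned recruitment.

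**4. The plan's own power figure.** Inputs from Section 10.4.1: difference 0.35, sigma 1, rho 0.2, M = 2, two-sided alpha 0.05.
- Variance of the mean of two measurements: (1 + 0.2)/2 = 0.6, so SD 0.7746.
- With 103 per group, SE = sqrt(2 × 0.6/103) = 0.1079; 0.35/0.1079 = 3.243; 3.243 − 1.960 = 1.283; power 0.9002. The plan's 0.90019 reproduces.
- 103/0.9 = 114.4, rounded up to 115. This also reproduces.

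**5. Chance imbalance by city.** The protocol gives no city split, so 25%, one third and 50% are assumed (58, 77 or 115 of 230 in one city), with one 115:115 list.
- SD of the count in one arm = sqrt(K × 0.25 × (230 − K)/229). For K = 115 this is 3.80, and the central 95% range is 50:65. For K = 58 it is 3.30.
- SD of the between-arm difference in city share = 2 × SD/115, which is 5.7 points (K = 58) to 6.6 points (K = 115).
- Probability of a difference of at least 10 points: 0.09 to 0.11. Of at least 15 points: 0.01 to 0.02.

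**6. What that does to the effect.** Assume that mean tests per three months differ between cities by g = 0.2 to 0.5. The chance shift has SD g × (SD of the share difference).
- Smallest: 0.2 × 0.0574 = 0.011; 1.96 SD = 0.02.
- Largest: 0.5 × 0.0661 = 0.033; 1.96 SD = 0.065.

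**7. What a city term gains.** It removes f(1 − f)g² from the variance of 0.6, where f is the share in one city.

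| f | g | Variance left | Power, 103 per group |
|---|---|---|---|
| 0.25 | 0.2 | 0.5925 | 90.4% |
| 0.25 | 0.5 | 0.5531 | 92.2% |
| 0.50 | 0.2 | 0.5900 | 90.5% |
| 0.50 | 0.5 | 0.5375 | 92.9% |

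**The case against.** A reader might infer that anyone with the protocol can regenerate all 230 assignments. The documents do not support that: the settings listed above are missing, the enrolment order would also have to be known, and this version postdates planned recruitment. Any exposure would be limited to staff who held the list, or the seed through an earlier version. Section 12.2 says that a protocol existed before the study began, but not whether that version carried the seed.

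The protocol also does not join the roles that selection would require. Section 5 names staff of the community organisations and participants as unblinded, while Section 6 gives identity checks to researchers and the eligibility record to the investigator. Nothing says that the assessors held the seed or list, and the extra checks apply only in case of doubt. This stands as a limit on the claim. It does not answer it, because nothing says that the assessors were kept from the list either.

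On city, a reader might infer bias. That does not follow. An unstratified 1:1 comparison is valid, and its standard error already reflects chance imbalance. The protocol does not show that city predicts testing; Section 7.3.2 says only that the messages list local testing locations. The kits are mailed, and baseline adjustment would absorb part of any city difference. The lack of strata is itself read from silence. What remains is a small gain in precision.

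**Conclusion.** The concealment point holds as a weakness in what Section 5 states. It prints the seed, software version and splitting tool, and describes no concealment step or independent list holder in an open-label trial with judgement at entry. Reconstruction by staff holding the seed is probable rather than demonstrated, and the documents give no evidence that allocation was predicted or entry influenced. Any resulting bias cannot be sized from the documents.

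The city point is one of precision and chance balance only. The chance shift (1.96 SD) is 0.02 to 0.065 against 0.35, and power rises from 90.0% to about 90.4-92.9%. These figures rest on the assumed city shares and differences, and on the plan's own sample-size variance without baseline adjustment. If baseline value already explains part of the city difference, the gain is smaller. No sample size changes.

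**What to change.** **Concealment (Section 5).** Take the seed out of the circulated protocol and keep seed and list with someone independent of recruitment. State that each assignment is released only after eligibility is recorded and the baseline questionnaire is submitted. If the list has not been used, generate a new one under an undisclosed seed. If enrolment is complete, report who held the seed and list, whether anyone judging eligibility had access, and how assignments were released. The cost is a few sentences, plus about half a day if a new list is made.

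**City (Section 10.3.2).** Add city as a factor in the primary analysis of covariance and in the mixed model, by dated amendment before analysis. Stratify the list by city if it has not yet been used. The cost is one sentence and one model degree of freedom. Section 14 expected analysis to finish before March 2022; if it has already been run, present the city-adjusted result as a supplementary analysis, labelled as added afterwards.
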